### Set-up of the training

The training is a group training consisting of seven three-hour sessions every two weeks. The last session takes place two month after the sixth session. The group comprises eight participants and one trainer. The trainer is experienced in working with groups, has psycho-therapeutic knowledge of the principles of rational emotive therapy as well as knowledge of occupational psychology and a basic understanding of chronic diseases and their consequences.

Participants are requested to read material from the textbook before each session, and to do homework that is discussed at the start of the following session. The exchange of experiences forms an important part of the training. Guest speakers are invited at three sessions. An actor is invited twice to assist with role-playing. An occupational physician and an employment expert are invited to discuss matters concerning work accommodations, sickness absence, disability pensions and other practical topics. In conjunction with the group sessions three individual consultations are offered: one at the beginning, one halfway through the training, and one after the sixth session. These consultations offer the trainer the possibility of giving feedback, and participants the possibility of discussing anything they want in private, or to pursue questions in greater depth.

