### Inclusion criteria

Participants are eligible for the study when they have a chronic physical disease, have a paid job, experience problems at work, fear losing their job or job satisfaction, and are willing to undertake actions to solve problems. Workers with predominant psychiatric conditions are excluded; people with a chronic physical disease in combination with depressive feelings are not excluded. Workers on long-term 100% sick leave that is expected to continue during the training are excluded.

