### Organisation of enrolment

Candidates apply by telephone. They can not be presented by others, (e.g. medical professionals). A first check at the moment of registration is on the objective inclusion criteria: chronic physical disease, paid job, and no long-term full-time sick leave. Candidates receive a written confirmation of their registration, explaining the procedures. Candidates receive the baseline questionnaire and the informed consent form three weeks before the randomisation. After a first and a second reminder, all participants who have returned the questionnaire are randomised.

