### Randomisation

Since not all questionnaires will be returned, the ideal group size is 18. If four or more persons have the same disease, randomisation is stratified on this disease, in order to prevent a coincidentally large group within the training group that shares the same disease. Randomisation is performed by the researcher in the company of another person, and with help of a computer program generating random numbers. Since ethical considerations preclude individual consultation before randomisation, persons randomised in the training group receive the invitation for a first individual consultation afterwards. If the trainer or the participant decide that the program does not meet the participants' expectations, a new randomisation procedure starts with the remaining persons in the control group.

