### Statistical analysis

Statistical analyses will be performed according to the intention-to-treat principle. Job retention will be analysed using survival analysis. The other variables will be analysed with repeated measurement analysis and mixed linear models.

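### Re-randomising controls into vacated training seats gives some people two allocations, which conflicts with the intention-to-treat analysis

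*Protocol article*

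**What the plan says.** All references are to the protocol article.

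- **Inclusion criteria.** Besides a chronic physical illness and paid work, candidates must have problems at work, "fear losing their job or job satisfaction, and are willing to undertake actions to solve problems".
- **Organisation of enrolment.** "A first check at the moment of registration is on the objective inclusion criteria": the illness, the job, and no prolonged complete sick leave. Everyone who then returns the baseline questionnaire is randomised.
- **Randomisation.** The article says that ethics rule out an individual consultation beforehand, so "persons randomised in the training group receive the invitation for a first individual consultation afterwards". Should either side conclude at that stage that the training falls short of what the person expects, "a new randomisation procedure starts with the remaining persons in the control group".
- **Set-up of the training.** "The group comprises eight participants and one trainer". The Randomisation section adds that, allowing for unreturned questionnaires, "the ideal group size is 18".
- **Statistical analysis.** "Statistical analyses will be performed according to the intention-to-treat principle".

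Nothing in the article says which allocation governs for a control who is drawn again, or whether the person who gave up the seat stays in follow-up and analysis.

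**The concern.** Intention-to-treat rests on one fixed allocation per person. The replacement rule gives redrawn controls a second one, triggered by a judgement made in one arm only, after allocation, by people who know the allocation. Fit is therefore tested individually in the training arm, while the people in the control arm who would also have declined are never identified.

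The consequence depends on the analysis chosen. If decliners are left out and replacements counted as trained, the training arm is a selected group set against an unselected one. If first allocation governs, the comparison is protected, but part of the control arm has been trained and power is lost. An analysis plan can settle which allocation counts. It cannot undo the training of people first allocated to control, because that is fixed by the randomisation procedure itself.

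**Working it through.** **The article's own figure.** Under Sample size and power, the cited end-point difference is 44.0 − 30.2 = 13.8 CIS points with SD 16.8, so 13.8/16.8 = 0.82 SD. For two-sided alpha 0.05 and 80% power, n = 2(1.96 + 0.84)²/0.82² gives 24 per arm. The t-test version gives 24.26, rounded up to 25, which is the stated figure. With the chosen 64 per arm, the effect detectable with 80% power is (1.96 + 0.84) × √(2/64) = 0.495 SD, or 8.32 points. The 0.5 SD used below is therefore roughly what 64 per arm can detect. The article does not state it as an expected effect.

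**Set-up.** Eight waves of (64 + 64)/8 = 16 randomised people, with eight seats per wave and each vacated seat refilled at random from that wave's controls. Assumed inputs: decline rate d of 10, 20 or 30%, and a prognostic gap g between decliners and others of 0.5 or 1.0 SD.

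**1. Decliners dropped, replacements counted as trained.** The trained group contains no would-be decliners, and the never-offered controls contain a share d. With no true effect, the expected difference is d × g:

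| d | g = 0.5 SD | g = 1.0 SD |
|---|---|---|
| 10% | 0.05 SD (0.84 points) | 0.10 SD (1.68 points) |
| 20% | 0.10 SD (1.68 points) | 0.20 SD (3.36 points) |
| 30% | 0.15 SD (2.52 points) | 0.30 SD (5.04 points) |

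Simulation agrees. The type I error is about 6–8% at 10% decline and about 8–17% at 20%. The sign follows the gap: if decliners would do better than average, the same analysis is biased against training.

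**2. Everyone analysed by first allocation.** Simulated bias is about 0 and type I error about 5%. A share 1 − d of the training arm is trained. Refilling all seats trains a share d of the controls. The contrast kept is (1 − d) − d = 1 − 2d. Without replacement it would be 1 − d. Power is from a two-sample t-test with 64 per arm and noncentrality effect × √32:

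| d | With replacement | Power | Without replacement | Power |
|---|---|---|---|---|
| 10% | 0.5 × 0.8 = 0.40 SD | 61% | 0.45 SD | 71% |
| 20% | 0.5 × 0.6 = 0.30 SD | 39% | 0.40 SD | 61% |
| 30% | 0.5 × 0.4 = 0.20 SD | 20% | 0.35 SD | 50% |

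At the cited 0.82 SD, the diluted effects are 0.66, 0.49 and 0.33 SD, and the same formula gives 96, 79 and 45%. Simulating trained and untrained people mixed within each arm, which widens the spread, gives 94, 74 and 43%. About 95, 75 and 45% is a fair summary.

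**3. Everyone ever offered a seat, decliners included, against never-offered controls.** Simulated bias is within about 0.01 SD and type I error 4–6%. The contrast kept is 1 − d, but the groups become unequal. Filling 64 seats takes 64/(1 − d) offers, so the never-offered controls number 64 − 64d/(1 − d), about 57, 48 and 37. Power for 0.5 SD is about 71, 58 and 43%.

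**The case against.** The strongest reply is that the article commits to intention-to-treat, and that analysis by first allocation is valid. This stands. A reader might infer that the rule breaks the randomised comparison whatever the analysis, or that no reading of the plan gives a sound answer. The documents do not support that: first allocation is unbiased though diluted, and ever-offered against never-offered is essentially unbiased too.

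A reader might also infer that a useless training would be made to look effective. That needs two things the article does not say: that decliners leave the analysis, and that they have the worse prognosis. The stated trigger is unmet expectations, which could equally describe people with milder problems.

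Nor does the article show that the subjective criteria go unchecked before randomisation. It calls the registration check a first one, and a questionnaire is returned before allocation. What can be said is that those criteria are not among the ones listed for the registration check, and that individual discussion of fit is placed after allocation, in one arm.

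Finally, a condensed article may leave the handling of decliners to a fuller document. That is fair for the analysis set. It does not cover the re-randomisation rule, which is stated outright.

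**Conclusion.** The point holds as a conflict between the Randomisation and Statistical analysis sections: a redrawn control has two allocations, and intention-to-treat needs one. The harm is conditional. Dropping decliners biases the result by about d × g, in a direction the article does not fix. Keeping first allocation avoids bias but costs power beyond what declining alone would cost: for a 0.5 SD effect, about 10, 22 and 30 percentage points at 10, 20 and 30% decline (71 − 61, 61 − 39, 50 − 20). At the cited 0.82 SD, power stays high at 10% decline but falls to about 45% at 30%. All these sizes rest on assumed decline rates and gaps, and on every vacated seat being refilled. With few decliners the effect is modest. The rule should still be changed, because it affects the comparison on every primary outcome and is cheap to remove.

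**What to change.** - Delete the re-randomisation rule. Randomise each person once and leave vacated seats empty.
- State that everyone randomised, decliners included, keeps receiving questionnaires and is analysed in the first allocated arm.
- Put the subjective eligibility questions (problems at work, fear of loss, willingness to act) to all candidates in the registration call or baseline questionnaire, before randomisation. This does not require the individual consultation that the article says ethics rule out, though it may not replace everything that consultation would bring out.
- For waves that have already used replacement, make first allocation the primary analysis. Report a complier (instrumental-variable) estimate, or ever-offered against never-offered, as supportive. Record each allocation, offer and refusal with its date.

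The cost is protocol wording, a few added questions and smaller groups. With empty seats, the average group is 8 × (1 − d), or about 7.2, 6.4 and 5.6 participants at 10, 20 and 30% decline. At the higher rates this is a real change to a training designed for eight, and the investigators should weigh it openly.

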### Outcome measures

Primary outcome measures are job retention, self efficacy, fatigue and work pleasure.

Not having a paid job, or having more than six months full-time sick leave in combination with the expectation that return to work is impossible or improbable is considered as job loss.

Self-efficacy is measured by a situation-specific instrument, measuring self-efficacy in solving work and disease related problems. It is developed according to the principles formulated by Bandura [32]. The fourteen items are measured on bipolar five-point Likert scales.

Fatigue is measured with the Checklist Individual Strength (CIS), a well-validated questionnaire for the working population [33]. It has four subscales: fatigue severity (8 items), concentration (5 items), motivation (4 items) and physical activity level (3 items).

Work pleasure is measured with a subscale of the Dutch questionnaire on Perception and Judgement of Work [34].

Secondary outcome measures are work-related problems, sick leave, quality of life, acquired work accommodations, burnout, and three quality of work measures: social relationships with colleagues and supervisor, and worries about work. These are subscales of the Dutch questionnaire on Perception and Judgement of Work [34].

Work-related problems are measured with eight items: having problems with specific work tasks, finishing work, arranging the workplace, commuting, communicating with colleagues, communicating with supervisors, accepting the disease, and balancing work and life at home. The three answer categories are counted as 0 (no), 1 (yes, slightly) or 2 (yes, severely) and are added up to an index measure.

Sick leave is measured as the number of days on sick leave during the last four months.

Quality of life is measured with the validated SF12 [35].

Work accommodations are measured with the Work Accommodations List [9].

Burnout is measured by the Utrecht Burnout Scale (UBOS) [36].

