If employed, many persons with chronic diseases experience problems at work. Lerner et al. [14] studied a large sample in the USA and concluded that, depending on the chronic disease, between 22% and 49% of the employees experienced difficulties in meeting physical work demands, and that between 27% and 58% had difficulty meeting psychosocial work requirements. Compared to healthy workers, chronically ill workers have higher scores on scales measuring fatigue and emotional exhaustion, which are correlated with perceived work stress [15,16]. Research focussing on the patients' perspectives provides insight into possible sources of stress and fatigue, and offers suggestions for remedies. Patients with diabetes, rheumatoid arthritis or hearing loss stated that important factors that helped them to continue working were the ability to cope with the illness, support from management and colleagues, and adequate work conditions [17]. A focus group study among employees with inflammatory arthritis reveals that they faced difficulties managing interpersonal and emotional difficulties at work, in addition to managing fatigue and other symptoms, and that they had trouble managing working conditions [18]. Asked what they expected in the way of work-related support, employees with multiple sclerosis mentioned support with managing work performance and support with managing social and personal expectations [19]. These findings suggest that vocational rehabilitation efforts should pay attention to psychosocial as well as practical bottlenecks at the workplace.

For the past several decades, social policy in many countries has been focussed on helping individuals with a chronic disease or handicap enter or re-enter the labour market, whereas less attention is paid to efforts aimed at helping employees to stay at work. Finding a new job is more difficult than trying to keep one, as one has the extra task of convincing a new employer of one's capabilities. This might be a reason to focus attention on structural vocational rehabilitation efforts aimed at job retention.

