A systematic review shows that there is some evidence for the effectiveness of interventions of this kind. However, the number and methodological quality of the studies is not sufficient to tell which one will be most successful [20]. Based on this review and discussions with experts, we developed training for employees with chronic diseases that supports them in solving practical and psychosocial problems. The aim is to prevent the unnecessary loss of their job.

The objective of this article is twofold. First, the development, set-up and contents of the intervention will be described. Second, we will specify the design of the study to evaluate its effectiveness.

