## Development and description of intervention

### Target group and purpose

This intervention is meant for employees with a chronic physical (i.e. not a predominant psychiatric) disease, who experience work-related problems and fear job loss or loss of work pleasure. We decided to include a wide variety of chronic diseases, such as musculoskeletal diseases like arthrosis and rheumatoid arthritis, neurological diseases like multiple sclerosis and Parkinson's disease. We included endocrinological diseases like diabetes, heart failure, pulmonary conditions, inflammatory bowel disease, chronic fatigue syndrome, and visual impairment, as well as any other chronic disease or handicap that results primarily in physical limitations. Work-related problems are broadly defined – they may be practical, social, mental or a combination of the three.

The aim of the intervention is twofold: job retention as well as maintenance or increase of work pleasure.

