## Discussion

Vocational rehabilitation interventions for persons with chronic diseases generally focus on entering or re-entering the labour market. Structured vocational rehabilitation interventions aimed at job retention are rare, notwithstanding demands for evidence-based vocational rehabilitation programmes aimed at preventing work disability for this group of employees [38]. Just a few of this kind of interventions could be traced in a systematic review [20]. A reason for this lack of initiatives or lack of documentation and evaluation might be that the societal consequences of work related problems are not felt clearly as long as people are still struggling to retain their jobs. However, when serious problems in work functioning finally result in long-term sickness absence, complete work disability or loss of a paid job, it is difficult to return to work.

The intervention we developed originates from an empowerment perspective and aims to help employees restore the balance of work capacity and work demands. We used a stepwise approach, starting with exploring practical, psychological or social problems, followed by communicating with the supervisor or others at work, and finally developing and implementing solutions.

Most studies on interventions aimed at job retention claim effectiveness. However, these claims are seldom underpinned with a study design offering strong evidence. Studies seldom use pretesting, a control group, a sufficient number of participants or a long-term follow-up. Our study design involves a control group and outcome assessments at five points over two years. We also try to include 128 participants randomised over two conditions.

An inevitable drawback is that participants are not blinded. The research project may trigger the awareness of the problems of participants, which can result in more than usual active coping behaviour in members of the control group.

The results of this study will generate knowledge about the nature of work-related problems and will possibly contribute to better vocational rehabilitation services for employees with chronic diseases. It will put issues at the crossroads of chronic disease and work, and of health care and occupational health on the agenda.

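### The job-loss rule has no exception for pension, so retiring at pension age counts as a failure in the primary job-retention outcome

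*Protocol article*

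**What the plan says.** The Outcome measures section of the protocol article states: "Primary outcome measures are job retention, self efficacy, fatigue and work pleasure". Job loss, the event for the first of these, is defined there by two routes: "Not having a paid job, or having more than six months full-time sick leave in combination with the expectation" of no likely return. The first route mentions no reason for being without work.

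The Background states the purpose of the training: "The aim is to prevent the unnecessary loss of their job". The section on target group and purpose adds: "The aim of the intervention is twofold: job retention as well as maintenance or increase of work pleasure".

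The Inclusion criteria begin: "Participants are eligible for the study when they have a chronic physical disease, have a paid job, experience problems at work". They go on to require fear of losing the job or job satisfaction, and willingness to act on problems. They name no upper age and no exclusion for planned retirement. Questionnaires follow at 4, 8, 12 and 24 months, and the Statistical analysis section assigns job retention to survival analysis.

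**The concern.** The aim is limited to losses that are unnecessary, but the event definition carries no such limit. A participant who reaches pension age during the two years has no paid job and so meets the first route, exactly as someone dismissed because of illness does. No training in communication or problem solving could have prevented that exit.

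Such events add to the count without carrying information about the training, and they pull the hazard ratio towards 1. Job retention is one of four primary outcomes and the sample size was not set for it, so it has little information to spare.

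**Working it through.** **1. The rule against the aim.**
- Aim (Background): prevent loss of the job that is unnecessary.
- Rule, first route (Outcome measures): no paid job, for any reason.
- Rule, second route: more than six months of full-time sick leave with no expected return.

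Retirement at pension age meets the first route and falls outside the aim. The second route only adds events, so it does not remove the mismatch.

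**2. Can it happen?** Eligibility requires a paid job at entry and states no upper age, and follow-up is 24 months. Anyone within two years of pension age can enter and become an event. How many would do so cannot be derived from the documents.

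**3. The plan's own figure.** The article gives no calculation for job retention. Its only calculated sample size concerns fatigue: difference 44.0 − 30.2 = 13.8, SD 16.8, alpha 0.05 (taken as two-sided), power 80%. The normal approximation gives 2 × (2.802 × 16.8 / 13.8)² = 23.3, so 24 per group. The t-test version gives 24.3, so 25, which reproduces the stated 25. It has no bearing on job loss.

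**4. Size of the dilution (assumed values).** Let q be the share of control-arm events that the training cannot affect (hazard ratio 1), and HR the true hazard ratio for the rest. With proportional hazards:

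observed HR = (1 − q) × HR + q

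Events for 80% power, two-sided 0.05 and equal arms, by Schoenfeld's formula: 4 × (1.960 + 0.842)² / (ln HR)² = 31.4 / (ln HR)².

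| q | Observed HR if true HR = 0.50 | Events needed |
|---|---|---|
| 0 | 0.50 | 66 |
| 0.10 | 0.9 × 0.5 + 0.1 = 0.55 | 88 |
| 0.20 | 0.8 × 0.5 + 0.2 = 0.60 | 121 |
| 0.30 | 0.7 × 0.5 + 0.3 = 0.65 | 170 |

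**5. In proportion.** Even with no dilution, 66 events would be 66 / 128 = 52% of all participants. If 10% to 15% of each arm lost work over two years (an assumption), there would be 6.4 to 9.6 events per arm, or about 13 to 19 in total. The comparison is short of events under any definition. The pension rule makes that somewhat worse but does not cause it.

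**The case against.** The strongest reply has three parts.

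- *Few retirees will enrol.* Participants must fear losing their job or job satisfaction, be willing to act, apply in person, and commit to a programme lasting several months. This selects against people about to retire. It stands as a reason to expect a small effect, but it does not change the rule.
- *An all-cause event is robust.* Participants are not blinded, and a self-reported reason for leaving could be coloured by arm. This is a fair argument against sorting exits by motive. It has much less force for pension, which is largely a matter of fact.
- *The detail may lie elsewhere.* Censoring rules belong in an analysis plan and the items in a questionnaire, and neither is shown. Their absence from the article is therefore no fault. The point is confined to the event definition that the article does state.

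A reader might also infer stronger faults that the documents do not support.

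- *That the rule looks only at paid-job status.* It does not, because the sick-leave route is part of the same definition.
- *That it wrongly treats a lost and replaced job as retention.* The Background does remark "Finding a new job is more difficult than trying to keep one", but in explaining why policy should attend to staying at work, not in defining the outcome. The Discussion speaks of "long-term sickness absence, complete work disability or loss of a paid job, it is difficult to return to work", so holding any paid work is a legitimate reading of retention.
- *That a dismissal followed by re-employment before month 24 would be missed.* This assumes that only status on the questionnaire date counts. The article does not say so, and in a survival analysis a recorded spell without paid work would be an event.
- *That counting exit by choice is an error.* Whether to reclassify it by self-reported motive in an unblinded trial is a debatable trade-off.
- *That the rule favours one arm.* Under randomisation, exits at pension age should fall on both arms alike. They dilute the contrast, and any imbalance is chance.

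**Conclusion.** The point holds in a narrow form. As written, retirement at pension age is a job-loss event, which does not match an aim limited to unnecessary loss. The consequence is attenuation: a true hazard ratio of 0.50 would appear as about 0.55 to 0.65 if 10% to 30% of control-arm events were beyond the training's reach. Both the hazard ratio and those shares are assumptions. The documents give no job-loss rate, age distribution or expected effect on retention, and the eligibility wording points to few such exits. This is a cheap improvement to a stated rule, not a flaw that invalidates the comparison. Loss of the baseline job despite re-employment, and chosen exit for other reasons, are at most matters for optional supporting analyses.

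**What to change.** Reword the first route so that the event is loss of paid work other than by pension. Say that this means retirement at pension age and not a disability pension, since leaving work through disability is the kind of loss the training is meant to prevent. In the existing follow-up questionnaires, record the date of leaving work and the reason, if this is not already done. In the survival analysis, censor pension exit or treat it as a competing event, and choose between the two before the data are examined. Keep the all-cause definition as a sensitivity analysis, so that the result can also be read without any attribution of cause.

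The cost is an item or two on questionnaires that both arms already receive, and one sentence in the definition. The downside is slightly fewer counted events and some reliance on self-report.
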